#### Monitoring adverse events

The NCI Common Terminology Criteria for Adverse Events (CTCAE) v4.0 will be used to characterize the toxicity profile of the study treatments on all patients. ECG assessments will be performed at screening, on Day 15 of Cycle 1, Day 1 and 21 of Cycle 2, Day 1 (± 3 days) of Cycle 3 and 5 and then on Day 1 (± 3 days) every 3 treatment cycles thereafter (Cycles 8, 11, 14, etc.). Dermatologic assessment will be performed at the beginning of Cycle 2 and then every 3 treatment cycles (± 3 days) thereafter (Cycles 5, 8, 11, etc.). Ophthalmologic examination is performed during treatment on suspicion of ocular toxicity. Left-ventricular function evaluation (MUGA) is evaluated throughout the study.

#### End of study and follow-up

The study will end when all patients enrolled have been followed for at least 3 years, withdrawal of consent, lost to follow-up, or the Sponsor decides to end the trial, whichever occurs first.

Patients may continue on study treatment until the development of progressive disease, unacceptable toxicity, and/or consent withdrawal. Patients who discontinue study treatment for any reason will be followed for development of squamous cell carcinoma, followed for disease progression and followed for survival until death, withdrawal of consent, or they are lost to follow-up.

### Statistical methods

#### Sample size calculation

Since ^18^F-FDG-PET scans are made at multiple time points (including baseline), the value of changes in metabolic activity can be studied in relation to overall response and time related endpoints.

There is a lack of evidence-based data in the assessment of therapy response and therapy resistance using ^18^F-FDG or ^18^F-FLT PET in patients with unresectable stage IIIc or metastatic melanoma treated with a BRAF inhibitor. Consequently, no robust power calculations can be performed to estimate samples sizes. However, given some feasibility aspects, some assumptions can be made about potential results and expected outcome. Based on recent publications [55, 56], it is expected that the PFS will be about 9 months. Assuming a hazard ratio of 0.5 or smaller and a 50–50 distribution in ^18^F-FDG PET positive and negative patients (either using the median or using the partial metabolic response of 25% reduction in the SUVmax) we can infer what median we would obtain.

Given the assumptions, the poor risk group would have a median PFS of 6.5 months and the good risk group a median of about 13 months. Assuming exponential survival, 18 months of accrual and another 18 months of follow-up (after the last patient has been enrolled), we would need to observe 66 events and 90 patients to enroll into the study (alpha 5% 2 sided and power 80%).

However, it should be stressed that these are assumptions and the nature of the study is explorative.

Experience with ^18^F-FLT is limited for monitoring response. Therefore, ^18^F-FLT will be ‘screened’ for its value by studying the association with ^18^F-FDG and CT in relation to response and outcome parameters. A review of studies looking at the value of PET in relation to response in various types of cancer, the average number of patients was 29 (data not shown, but available on request). The number of 25 patients is therefore considered both feasible and sufficiently valuable.

Important issues to solve in this series of patients are to develop a sensitive cut- off value for metabolic response (which may be different than the median or the cut-off for metabolic response found in other diseases), the association or potentially added value of the ^18^F-FLT PET-scan and the association with (high-dimensional) biomarkers.

Biopsies will be performed in a subset of 40 patients. This number is based on the paper of Dobbin and Simon 2007 in which sample sizes are calculated for building predictors [57]. The simulations indicated that with 2 differentially expressed genes, and 40 patients an effect size (2δ/σ) of 1.5 or more and with one differentially expressed gene, an effect size of 1.7 or better could be obtained.

#### Statistical analysis

Patient demographic data, tumor characteristics and data derived from the scans and biopsies will be described in frequency tables. In general, for continuous variables, mean, standard deviation, median, IQR and minimum and maximum will be given. Categorical variables will be presented with 95% confidence intervals whenever relevant (i.e. response).

SUV-parameters (mean, 3D peak, max) for ^18^F-FDG and ^18^F-FLT will be measured on a continuous scale and categorized or dichotomized using various rules available (PERCIST, and published disease specific rules). CT will be expressed according to RECIST v1.1. Linear-by-linear non-parametric analysis will be used for associations between ^18^F-FDG and ^18^F-FLT PET imaging and pharmacokinetics parameters and ceCT. Logistic regression and ROC-analysis may be applied to investigating the continuous parameters in association with response (CR + PR)/non response or clinical benefit (CR + PR + SD)/progression. Accuracy measures and best cut-off values will be calculated for each separate time point (Day 15 of Cycle 1 and Day 21 of Cycle 2 respectively). Whenever applicable and possible, baseline values (of ^18^F-FDG and ^18^F-FLT and pharmacokinetics parameters) will be included as separate (fixed) covariables.

A series of analysis will be performed to study PET imaging compared to ceCT, currently considered the ‘gold standard’. Agreement of test results will be evaluated using Bland- Altman plots and results will be expressed in terms of bias and precision measures with corresponding confidence limits. Both ceCT and PET data (i.e. baseline, decrease) will be associated with PFS and OS by means of survival model predictive accuracy analysis (cox regression) to obtain estimates of (time-dependent) sensitivity and specificity, and (time-dependent) receiver operating characteristic (ROC) curves [58–60]. Survival estimates will be plotted in Kaplan-Meier curves and tabulated with 95% confidence intervals at fixed time points and at its median (including 95% confidence interval).

Log-rank tests will be used for comparing different groups with respect to survival outcomes. Cox-proportional hazard analysis will be used to calculated hazard ratios and to model survival in the presence of potential imbalances or confounders.

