### Response monitoring with PET

For monitoring therapy response in unresectable stage IIIc or metastatic melanoma, contrast enhanced CT (ceCT) is the current standard imaging tool. Unfortunately, reduction in tumor size cannot be assessed within days after the initiation of therapy and anatomic size does not provide information about the development of therapy response or resistance at a molecular level. It has been clearly demonstrated that alterations in metabolism occur earlier than anatomical size reduction after the initiation of therapy. PET imaging is a sensitive method to detect alterations in cell metabolism, even within 15 days after the start of therapy [30]. By detecting these metabolic alterations, it is suggested that responders can be distinguished from non-responders at an earlier phase compared with anatomical imaging with ceCT [31]. This way, unnecessary expensive treatment with combined BRAF/MEK inhibition and its side effects may be prevented in patients who will not benefit from this therapy.

^18^F-FDG PET in monitoring response assessment has been investigated in many tumors, but has not been studied systematically in metastatic melanoma patients, due to the lack of an efficacious treatment. With the promising results in OS and PFS in patients treated with combined BRAF/MEK inhibition, response monitoring becomes a topic of high interest. Sondergaard et al. studied the effect of vemurafenib in different in-vitro cell lines, all with a BRAFV600 mutation [32]. They demonstrated a different sensitivity to PLX4032 in all ten cell lines, three of these cell lines even showing resistance. Inhibition of ^18^F-FDG uptake in the cell lines was more profound in the sensitive cell lines than in the resistant cell lines, suggesting that ^18^F-FDG PET can be used as a non-invasive imaging technique to distinguish between sensitive and resistant tumors.

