### Study objectives

The primary aims of this study are to evaluate whether changes in ^18^F-FDG and/or ^18^F-FLT PET in the first 7 weeks can predict progression-free survival and whether early changes (at 2 weeks) in ^18^F-FDG and/or ^18^F-FLT PET can be used for early detection of response to treatment with combined BRAF/MEK inhibitor vemurafenib plus cobimetinib compared to standard response assessment with ceCT according to RECIST v1.1 at 7 weeks.

Several secondary aims are defined in this study. The level of target inhibition is studied to whether it can predict the type (CR/PR, SD or PD) and duration of response. Molecular mechanisms of resistance will be elucidated by integrating global protein phosphorylation, genomic and cancer mutation data. The correlation between PET imaging and several key tumor characteristics at different levels is studied through a) measurements of BRAF signaling activity by immunohistochemistry (including pERK), b) analyzing DNA mutation spectrum by next-generation sequencing, c) analyzing gene expression patterns by microarray analysis and d) analyzing protein phosphorylation patterns by mass spectrometry-based phosphoproteomics. We will investigate whether differences in global phosphoprotein (including markers of BRAF pathway activity) and mutation profiles occur between sensitive and matched resistant tumor lesions and whether these profiles can predict benefit from vemurafenib/cobimetinib and resistance. Furthermore, we will investigate whether differences in protein phosphorylation patterns can be identified between pre and post treatment tumor biopsies, and whether the pre-treatment patterns would bare predictive power for response to treatment. The correlation between the pharmacokinetics of vemurafenib/cobimetinib and PET imaging is studied as well as the correlation between pharmacokinetics and therapy response. Finally, various quantitative measures of radiotracer uptake from baseline upon PET imaging are studied for predicting the type (CR/PR, SD or PD) of response, progression-free survival and overall survival.

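### Bland-Altman bias and limits are named as the agreement analysis for PET against ceCT, but the two measure different quantities, so the result would not show disagreement about response

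*Protocol article*

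**What the plan says.** The relevant text is in the Statistical analysis section of the protocol article. One paragraph opens with "A series of analysis will be performed to study PET imaging compared to ceCT" and calls ceCT the current reference standard. Its next sentence fixes the agreement method: "Agreement of test results will be evaluated using Bland- Altman plots and results will be expressed in terms of bias and precision measures", with confidence limits. That paragraph names no other pair of methods.

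The preceding paragraph defines the two measurements. SUV parameters (mean, 3D peak, max) "will be measured on a continuous scale and categorized or dichotomized using various rules available (PERCIST, and published disease specific rules". For the other modality, "CT will be expressed according to RECIST v1.1".

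Study objectives makes the comparison part of a primary aim: early PET change, at 2 weeks, is to be judged "compared to standard response assessment with ceCT according to RECIST v1.1 at 7 weeks".

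The Statistical analysis section plans other PET-ceCT analyses too:
- "Linear-by-linear non-parametric analysis will be used for associations between" PET imaging, pharmacokinetic parameters and ceCT;
- logistic regression and ROC analysis against response or clinical benefit, as an option;
- accuracy measures and cut-offs, as a commitment, at Day 15 of Cycle 1 and Day 21 of Cycle 2;
- time-dependent sensitivity, specificity and ROC curves for PFS and OS, using both modalities.

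No agreement measure for paired response categories is named.

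**The concern.** A Bland-Altman plot shows the difference between two measurements against their mean. The average difference can be called bias, and the limits can be read as imprecision, only if both methods estimate the same quantity in the same units. SUV is tracer uptake; RECIST v1.1 yields lesion size or an ordered category.

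The article's own rationale says that the two should differ. Response monitoring with PET states that "alterations in metabolism occur earlier than anatomical size reduction after the initiation of therapy" and that "anatomic size does not provide information about the development of therapy response or resistance at a molecular level". A systematic gap between SUV change and size change is what the study hypothesis predicts, yet the plan would report it as bias against the reference standard.

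At stake is the reading of the agreement result. PET could match ceCT on every patient's response and still appear biased with wide limits. The question that matters, whether the two scans put the same patients in the same response group, would have no agreement statistic.

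**Working it through.** **Figures in the plan.** The article gives no figure for the agreement analysis. Its only sizing figure, 66 events, belongs to the PFS comparison of PET-defined groups. It reproduces with Schoenfeld's formula: 4 × (1.960 + 0.842)² / (ln 0.5)² = 4 × 7.849 / 0.4805 = 65.3, rounded up to 66. It does not depend on the Bland-Altman analysis.

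**Step 1: what could enter the plot.** The article does not say, so each option is taken in turn.
- *Raw values.* SUV and lesion diameter have different units and cannot be subtracted.
- *Categories.* CR, PR, SD and PD are ordered labels. A difference between a metabolic label and a RECIST label has no numerical meaning.
- *Percentage change on both sides.* The units now match, but one is change in uptake and the other change in size. For the 2-week aim the pair also differs in time: PET at 2 weeks, ceCT at 7 weeks.

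Only the third option can be computed, so the next two steps test it.

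**Step 2: identical classification.** Assumed values, not from the documents: each responder has a 60% fall in SUV and a 35% fall in diameter; each non-responder 10% and 0%. The response rate of 68% is the one that the Background gives for the combination in coBRIM. Any PET cut-off between a 10% and a 60% fall (including the 25% fall in SUVmax mentioned under Sample size calculation), paired with any CT cut-off between a 0% and a 35% fall, separates the same patients. Classification agrees in 100%.
- Difference, SUV change minus diameter change: responders -60 - (-35) = -25; non-responders -10 - 0 = -10.
- Bias: 0.68 × (-25) + 0.32 × (-10) = -17.0 - 3.2 = **-20.2 points**.
- SD of the difference: 15 × √(0.68 × 0.32) = 7.0.
- Limits: -20.2 ± 1.96 × 7.0 = **-33.9 to -6.5**.

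**Step 3: identical ranking, continuous changes.** Assumed: SUV change has mean -60% and SD 25, with values beyond ±100% set to ±100%. Size change is exactly k times SUV change, so the correlation is 1.0. For every PET cut-off c, the CT cut-off k × c picks the same patients. The difference is (1 - k) × SUV change, and its slope on the mean is 2(1 - k)/(1 + k). A simulation of 200,000 patients gives:

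| k | Bias (points) | Limits | Slope of difference on mean |
|---|---|---|---|
| 1/3 | -39.7 | -70.7 to -8.6 | 1.00 |
| 1/2 | -29.7 | -53.0 to -6.5 | 0.67 |
| 2/3 | -19.8 | -35.3 to -4.2 | 0.40 |

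The bias depends on k, the ratio of size change to uptake change, and not on any discordance, because there is none. The non-zero slope also means that a single bias figure does not describe the difference across the range of change.

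**The case against.** The strongest counter-argument is that the PET-ceCT comparison does not rest on this plot. The primary aim asks whether early PET change can detect response, with ceCT by RECIST as the reference. That is a diagnostic-accuracy question, and the same section commits to accuracy measures and cut-offs at both time points and to linear-by-linear association. It allows ROC analysis against response, and it plans time-dependent ROC for PFS and OS using both modalities. Study endpoints also lists diagnostic accuracy in responders and non-responders. This stands. A reader might infer that the primary aim is left unanswered, or that it rests on an uninterpretable number; the documents do not support that.

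Second, the article is condensed and does not say which variables enter the plot. A reader might infer that RECIST categories will be subtracted from one another; the text does not say so. This softens the point but does not remove it, because the method is named and attached to PET against ceCT, and no reading of the stated measurements gives two estimates of one quantity. Metabolic Tumor Volume, a secondary endpoint, is the PET measure nearest to size, but CT is to be expressed by RECIST.

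Third, the study is described as explorative, and no sample size or decision rule uses this analysis. That limits the consequence. An exploratory estimate must still be interpretable.

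Fourth, the size rests on assumed changes. That is so. The figures show that mean difference and classification agreement are separate things; they do not predict the trial's result.

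**Conclusion.** The point holds for the agreement analysis only. As written, Bland-Altman bias and limits for PET against ceCT would not measure disagreement about response. In the illustrations, with identical classification or ranking, the bias lies between about -20 and -40 percentage points. The sizes rest on assumed SUV and diameter changes, with only the 68% response rate taken from the article. The conclusion that the method does not fit rests on the article's own definitions of the two measurements and on its statement that metabolism changes before size.

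The wider primary aim remains addressed by the accuracy, ROC and survival-prediction analyses. Those analyses do not, however, supply a named measure of agreement between paired metabolic and RECIST categories. That is the gap left once Bland-Altman is set aside.

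**What to change.** For PET against ceCT, replace the Bland-Altman sentence with:
1. A cross-table of metabolic response category (PERCIST) against RECIST v1.1 category at each PET time point, stating which ceCT it is paired with (the primary aim names the 7-week scan), with weighted kappa and 95% confidence interval.
2. With ceCT as the reference, sensitivity and specificity of the dichotomised PET call, with 95% confidence intervals. This makes the accuracy measures already planned explicit.
3. Optionally, a rank correlation with confidence interval between percentage SUV change and percentage change in sum of diameters. It mainly adds an effect size to the planned association test.

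McNemar's test should not stand in for item 1: it compares marginal rates and can be non-significant when many patients are discordant in balanced directions. For ^18^F-FLT the tables would have at most 25 patients and one early time point, so their intervals will be wide.

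Keep Bland-Altman for same-quantity comparisons, such as repeat reads of one SUV measure.

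Cost: a change of wording in the protocol or analysis plan. The PERCIST and RECIST categories are already planned, so no new data, visits or patients are needed.

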### Study procedures

The schedule of study assessments and procedures are detailed in Table 2.

**Table 2 Tab2:** Schedule of assessments and procedures

Period	Screening	Baseline study procedures			Vemurafenib/ Cobimetinib Treatment Period									Follow-up after treatment
Cycle	Within 28 days before start therapy	Within 14 days before start therapy	Cycle1			Cycle2		Cycle3	Cycle4	Cycle5	Cycle6	Cycle7+	At progression (EoS)	Every 12 weeks
Day			1	14	15	1	21	1 (± 3)	1 (± 3)	1 (± 3)	1 (± 3)	1 (± 3)	Within 7 days (on therapy)	
In- and exclusion criteria	**X**													
Medical history and demographics	**X**													
Interval medical history		**X**			**X**	X	**X**	X	X	X	X	X	**X**	X
Physical examination	**X**	**X**			**X**	X	**X**	X	X	X	X	X	**X**	X
Vital signs (Temp, HR, RR)		X			X		X	X	X	X	X	X	X	
Pregnancy test (if indicated)	**X**													
Dermatologic examination	X					X				X		X		X
Ophthalmologic examination	if indicated													
MUGA scan	X					X				X		X	X	
12-lead electrocardiography (ECG)	X	X			X	X	X	X		X		X		
Contrast Enhanced CT (CECT)	X	**X**			**X**		**X**		X		X	X	**X**	
ECOG performance status	**X**	**X**			**X**	X	**X**	X	X	X	X	X	**X**	X
Blood samples	**X**	**X**			**X**	X	**X**	X	X	X	X	X	**X**	
Informed consent	**X**													
PK blood sample		**X**			**X**								**X**	
DNA blood sample (Substudy 1 and 2)		**X**											**X**	
^18^F-FLT PET (Substudy 1)		**X**		**X**									**X**	
^18^F-FDG PET		**X**			**X**		**X**						**X**	
Tumor biopsy (Substudy 1 and 2)		**X**			**X**								X	
Adverse events		**X**			X	X	X	X	X	X	X	X	X	X
Start vemurafenib cobimetinib			X											

**X** *= Assessment/procedure performed to meet the objectives of the study,* X = *Assessment/procedure performed to monitor vemurafenib/cobimetinib treatment*

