#### Response assessment

Tumor response will be evaluated with ceCT scans of neck, thorax, abdomen and pelvis according to RECIST v1.1. Any evaluable and measurable disease must be documented at screening and re-assessed at each subsequent tumor evaluation. The ceCT scans are performed at baseline, 2 weeks after start study medication, at the end of the seventh week, every 8 weeks thereafter and at progression following standard protocol. CT/MRI scans may be repeated at any time if progressive disease is suspected.

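### Week-7 PET and ceCT changes are related to PFS and OS without a landmark, so progressions found on the scan day can count as predicted events

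*Protocol article*

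**What the plan says.** Study objectives makes it a primary aim to learn whether PET changes over the first 7 weeks predict PFS. For this, Statistical analysis states: "Both ceCT and PET data (i.e. baseline, decrease) will be associated with PFS and OS by means of survival model predictive accuracy analysis". The methods named are Cox regression, time-dependent sensitivity, specificity and ROC curves, Kaplan-Meier curves and log-rank tests. The section gives no time origin for PFS, no landmark, and no rule for patients who progress before or at the scan.

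The section on PET imaging places FDG PET at baseline, Day 15 of Cycle 1, Day 21 of Cycle 2 and progression. Response assessment says of the CT: "The ceCT scans are performed at baseline, 2 weeks after start study medication, at the end of the seventh week, every 8 weeks thereafter". Table 2 puts ceCT and FDG PET in the same visit columns.

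Sample size calculation applies PFS medians to PET-defined groups: "the poor risk group would have a median PFS of 6.5 months and the good risk group a median of about 13 months". It counts accrual and follow-up from enrolment and concludes that "we would need to observe 66 events and 90 patients to enroll into the study". No event is set aside as falling before or on the day of the scan.

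**The concern.** The predictor is a post-baseline measurement, and the event is declared by a CT at the same visit. Apart from extra scans for suspected progression, no ceCT is scheduled between week 2 and week 7. Most progressions in that interval are therefore recorded at the week-7 visit, on the day the week-7 PET value is obtained. Counting them as outcomes of that PET mixes diagnosis with prediction. For ceCT the overlap is closer still: in a patient read as progressive at week 7, the reading is both predictor and event.

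This can inflate the week-7 association and the time-dependent AUC, and can tilt the PET-versus-ceCT comparison towards ceCT. The study also wants to derive a cut-off for metabolic response. A cut-off tuned partly on progressions already visible on the same day's CT would look predictive without giving any lead time.

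**Working it through.** **Inputs (Sample size calculation).** Hazard ratio 0.5, groups 50:50, two-sided alpha 5%, power 80%; exponential PFS with medians 6.5 and 13 months; 18 months of accrual plus 18 months of follow-up; 90 patients, so 45 per group. Day 21 of Cycle 2 is day 28 + 21 = 49, or 49/30.44 = 1.61 months. Day 15 is 0.49 months.

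**1. The plan's own figure.** Schoenfeld: (1.960 + 0.842)² / (0.25 × (ln 0.5)²) = 65.35, so 66 events. This reproduces the plan.

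**2. Total expected events.** P(event) = 1 − [exp(−λF) − exp(−λ(A+F))]/(λA), with A = F = 18 and λ = ln 2/median. This gives 93.5% (poor) and 75.4% (good). Events: 45 × 0.935 + 45 × 0.754 = 76.0.

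**3. Events by each scan.** P = 1 − exp(−ln 2 × t/median).

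| Scan | Poor | Good | Events in 90 |
|---|---|---|---|
| Day 15 | 5.1% (2.3) | 2.6% (1.2) | 3.5 |
| Day 49 | 15.8% (7.1) | 8.2% (3.7) | 10.8 |

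Between the two scans: 10.8 − 3.5 = 7.3, so about 7 progressions would be found at the week-7 visit.

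**4. Bias from those 7.** Simulation of 1,500 trials per setting: 7 events placed on day 49 and no PET effect afterwards. Hazard ratios are PET-poor versus PET-good; the plan's 0.5 is 2 on this scale.

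| Share of the 7 in the PET-poor half | Apparent HR | Two-sided false positives |
|---|---|---|
| 75% | 1.11 | 7.5% |
| 90% | 1.17 | 10.3% |
| 100% | 1.21 | 12.2% |
| Any, with landmark | 1.00 | about 5% |

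At a 50% share there is no bias. A second, smaller simulation (200 runs per setting) took all scan-day progressors as PET non-responders and varied their number. With 3, 5 or 10 of them, the HR of responders versus non-responders was 0.92, 0.88 or 0.77. Inverted, these are 1/0.92 = 1.09, 1/0.88 = 1.14 and 1/0.77 = 1.30.

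**5. Power after a week-7 landmark.** At risk: 90 − 10.8 = 79.2 (37.9 poor, 41.3 good; poor share 0.479). Later events: 76.0 − 10.8 = 65.2. Power = Φ(√(65.2 × 0.479 × 0.521) × 0.693 − 1.960) = Φ(0.84) = 79.8%. If analysis is triggered at 66 total events, 66 − 10.8 = 55.2 are usable and power is 73.0%. For Day 15 the corresponding figures are 72.5 events (83.9%) and 62.5 events (78.2%).

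**6. Range for the early rate.** The documents give none. Assuming 2% to 15% progress by week 7 gives 2 to 14 events, and power of 79% to 71% if the total stays at 66.

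**The case against.** The strongest reply is that this is a condensed article, and that a time origin and a landmark rule may stand in the full protocol or analysis plan. Nothing in the text says that scan-day events are counted as predicted. That stands as a caution: the counting is what follows if the article's description is applied as written. It does not remove the point. The article sets out the primary-aim models in some detail, and its sizing treats a PET grouping as known at enrolment.

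A reader might also infer that every progression before the scan is counted as predicted. The documents do not support this. A patient who progresses and stops before week 7 has no week-7 PET and leaves that model. Such a patient enters only if treatment continues past progression, for which Study medication leaves room, or if the progression PET is substituted, which the plan does not state. Among scanned patients, moving the origin by 7 weeks leaves the Cox hazard ratio and log-rank test unchanged. The guaranteed event-free time shifts only Kaplan-Meier medians and ROC time horizons.

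Three further limits hold. For the Day 15 PET, a week-7 progression is a legitimate later event, so little changes there. The week-7 CT defines an event only in patients read as progressive. The size of the bias rests on an assumed clustering of early progressors among PET non-responders.

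**Conclusion.** The point holds for progressions found at the week-7 visit. With no landmark stated and the ceCT on the same day as the PET, about 7 of 90 patients could supply concurrent events to the week-7 models. That count rests on extending the plan's exponential curves back to the start of treatment. If 75% to 100% of these patients are PET non-responders and PET has no later effect, the apparent HR is about 1.1 to 1.2 and two-sided false positives about 7% to 12%. With no clustering there is no bias. The inflation is modest beside a design effect of 2, but it favours a positive finding and falls unequally on PET and ceCT.

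A reader might conclude that the primary analysis is invalid and that this must be corrected before anything else. The documents do not support that: Trial design and Sample size calculation both call the study explorative, and the Day 15 predictor is barely touched. It should be fixed, at moderate weight.

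**What to change.** For each scan time point (Day 15 of Cycle 1 and Day 21 of Cycle 2), start PFS and OS at that scan. Include only patients who are alive and progression-free after that visit's ceCT. Use this set and clock for Cox, Kaplan-Meier, log-rank and time-dependent ROC, and for PET and ceCT alike. Report the progressions up to and including the scan day separately, with their number, in the RECIST accuracy analysis, where same-day agreement is the proper question.

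The cost is wording plus about 11 events lost from the week-7 model. Power stays near 80% (65 events) only with full follow-up and no loss. If the analysis is triggered at 66 total events, about 55 are usable and power is about 73%. The plan should therefore analyse at full follow-up or restate the power. Waiting looks feasible, since End of study and follow-up foresees at least 3 years per patient, against the 18 months after last enrolment used for sizing.
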